**Methods:**

This is a feasibility randomized controlled trial. We plan to recruit a total of 36 community-dwelling older adults using purposive sampling. Participants will be randomized 1:1 to either the intervention or the control group. The intervention group will be asked to engage with KOKU-Nut 3 times a week for 12 weeks. Participants in the control group will receive a leaflet promoting a healthy lifestyle. All study participants will complete questionnaires at baseline and the end of the 12 weeks. A sample of participants will be asked to participate in an optional interview. The study will collect a range of data including anthropometry (height and weight), dietary intake (3-day food diary), physical function (grip strength and 5-times sit-to-stand), perceived quality of life (EQ-5D), usability (System Usability Scale), and safety (adverse events).

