Secondary outcomes will consider the usability and safety of the intervention and the practicality of collecting and assessing the effectiveness of KOKU-Nut compared to an information booklet about healthy living. The perceived usability of KOKU-Nut will be assessed using the validated 10-item system usability scale. Responses are measured on a 5-point Likert scale ranging from 1 (strongly disagree) to 5 (strongly agree). A score >68 is considered above-average usability and >80 is considered high usability such that participants are likely to recommend the product to peers. The safety of the intervention will be based on the number of adverse events that occurred as a result of participation in the study. We will consider the practicality of collecting effectiveness data by documenting the amount and rationale for any missing data. Changes in means and SDs will be compared to consider the preliminary effectiveness of the intervention and to calculate sample sizes for a future trial. The study will be assessed against progression criteria based on Shanyinde et al [21] to determine progression to a powered RCT. Figure 1 shows the schedule of the intervention and assessment according to the SPIRIT statement.

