### Sample Size

As this is a feasibility study that is not designed to detect statistically significant differences in measures, no formal power calculation has been conducted to determine the sample size. Lancaster et al [22] recommend a sample size of 36 participants for feasibility and pilot studies, so after accounting for potential dropout (at 20%), we aim to recruit 18 participants in each arm.

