### Statistical Analysis

All quantitative data will be analyzed in STATA (version 15; StataCorp). The primary outcome will be calculated with regard to the indicators of feasibility to investigate engagement with the intervention, recruitment and retention rates, and acceptability of the intervention and study design. These will be summarized appropriately using descriptive statistics including percentages, mean with SDs, and ranges. Pre-post intervention changes in health measures will be analyzed in an exploratory fashion to gain preliminary insights into the number of valid versus missing data and to assess how outcomes are associated with group assignment and intervention engagement. Effect sizes will be determined using Cohen *d* to calculate sample sizes for a powered RCT.

Qualitative interview transcripts will be managed using NVivo software (version 12; QSR International Pty Ltd) and analyzed using an inductive approach with the 5 stages of framework analysis [34,35] to understand any barriers to the recruitment process, the suitability of the assessment measures, and the practicality of using the KOKU-Nut intervention. The first stage of framework analysis involves familiarization of the data from the transcripts and audio-recordings. The second stage involves classifying the data into codes and identifying a thematic framework from the key themes identified. The third stage involves systematically indexing the data using the framework identified. The fourth stage involves charting and synthesizing the data to categorize and capture key concepts and themes. The final stage involves the mapping and interpretation of the data [34]. All stages of the analysis process will be discussed and reviewed with at least 2 researchers (ES and SB) to ensure rigor [36].

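### The powered RCT is to be sized from this trial's observed effect, but with about 14 completers per arm Cohen d carries a 95% CI of about ±0.73, too imprecise for a design target

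*Protocol article*

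**What the plan says.** The Statistical Analysis section of the protocol article closes its quantitative paragraph with a rule: "Effect sizes will be determined using Cohen" d, and the stated reason is "to calculate sample sizes for a powered RCT". The Outcomes section says much the same: "Changes in means and SDs will be compared to consider the preliminary effectiveness of the intervention and to calculate sample sizes for a future trial".

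Under Sample Size, the article describes the study as "not designed to detect statistically significant differences in measures" and says that "no formal power calculation has been conducted to determine the sample size". It gives the target as "we aim to recruit 18 participants in each arm", with a 20% dropout allowance.

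The article names no minimum worthwhile difference, no interval around d and no other safeguard for the sizing step.

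**The concern.** Sample size varies with 1/d², so an error in d is magnified in the planned size: halving d quadruples n. A trial of this size estimates its SD and its retention tolerably well, but it estimates the difference between arms poorly. Cohen d puts that poorly estimated difference into the numerator of the design target.

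If the point estimate is used as written, the next trial's size will be driven largely by chance. A high draw gives an underpowered trial. A low draw gives one several times larger than needed, and a zero or negative draw gives no usable size. Preparing a powered RCT is what this study is for, so this handover matters even though effect size is only a secondary aim.

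**Working it through.** **Inputs from the article.** 18 recruited per arm and 20% dropout (Sample Size); 1:1 allocation (Abstract, Methods).

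**Inputs assumed, because the article does not give them.** Two-sided α of 5%; power of 90%; true d of 0.3 or 0.5; normally distributed outcomes; the same standardiser in both trials; the observed d entered directly into the usual formula.

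**Step 1, the article's own figure.** There is no power calculation to reproduce. If 36 were the number needed after dropout, recruitment would have to be 36/0.8 = 45. The 36 therefore fits only as the number recruited, which leaves 18 × 0.8 = 14.4 completers per arm (28.8 in all). The wording leaves this open, so both 14.4 and 18 per arm are carried forward.

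**Step 2, precision of d.** For n per arm, SE(d) = √(2/n + d²/(4n)).
- n = 14.4, d near 0: SE = √(2/14.4) = 0.373; half-width 1.96 × 0.373 = 0.73.
- n = 18, d near 0: half-width 1.96 × √(2/18) = 0.65.
- n = 14: half-width 0.74 at d = 0 and 0.75 at d = 0.5.

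At 14 per arm, an observed d of 0.5 has a 95% CI of −0.25 to 1.25, and an observed 0.3 has −0.44 to 1.04. Exact noncentral-t limits agree to within 0.01.

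**Step 3, what that does to the next trial's size.** n per arm = 2 × ((1.96 + 1.2816)/d)² at 90% power.

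| d | n per arm, 90% power | n per arm, 80% power |
|---|---|---|
| 0.2 | 526 | 393 |
| 0.3 | 234 | 175 |
| 0.5 | 85 | 63 |
| 0.8 | 33 | 25 |
| 1.25 | 14 | 11 |

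An observed d of 0.5 would give 85 per arm at 90% power. Its CI covers 14 per arm at the upper limit and 526 at d = 0.2, with no finite size once d reaches 0.

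**Step 4, how often the plan goes wrong.** 200,000 simulated feasibility trials, 14 per arm, 90% power for the next trial:

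| | True d = 0.3 (234 per arm needed) | True d = 0.5 (85 per arm needed) |
|---|---|---|
| Observed d ≤ 0 | 21% | 9% |
| Size wrong 3-fold or more, counting d ≤ 0 | 66% | 47% |
| Next trial's true power < 80%, all simulated trials | 46% | 43% |
| Same, only where observed d > 0.1 | 65% | 50% |

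With 18 per arm and true d = 0.3, the size is still wrong 3-fold or more in 61%.

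**Hand check for true d = 0.3**, using SE = √(2/14) = 0.378:
- P(d ≤ 0) = Φ(−0.3/0.378) = Φ(−0.79) = 21%.
- The size is 3-fold too small when d > 0.3 × √3 = 0.52, with probability 28%. It is 3-fold too large, or undefined, when d < 0.3/√3 = 0.173, with probability 37%. The sum is 65%.
- Power falls below 80% when d > 0.3 × (3.2416/2.8016) = 0.347, with probability 45%.

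These match the simulation to within about one percentage point. The 3-fold figures do not depend on the chosen α or power, because both cancel in the ratio of planned to needed size.

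**The case against.** The strongest reply is that estimating preliminary effect sizes is an ordinary feasibility aim, that the article calls the analysis exploratory, and that the Outcomes section names SDs, which are a proper input to a sample size. All of that stands. Reporting group differences is not at fault, and the SDs should be kept. None of it removes the sentence under Statistical Analysis that assigns Cohen d to the sizing step. Because the article fixes that choice itself, it is not a detail left to a fuller analysis plan.

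Three stronger readings are tempting, and the documents do not support them.

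- A reader might infer that the error selects itself: a powered trial would follow only when d happens to be large, so it would nearly always be too small. Nothing in the article makes progression depend on the observed d. The Outcomes section points to separate progression criteria from a cited source, whose content is not shown, and the primary outcomes are engagement, recruitment, retention and acceptability. For the same reason the 65% and 50% figures, which keep only trials with an observed d above 0.1, should not be the headline. That cut-off was chosen for this check; the unconditional 46% and 43% are the fair ones.
- A reader might see a contradiction between the sizing rule and the statement in Sample Size that the study is not built to detect differences. There is none: a study can estimate an effect without being powered to test it. The problem is imprecision alone.
- A reader might conclude that the present trial is compromised. It is not. Sizing comes later and touches no allocation, data collection, safety measure or feasibility result. It can also be corrected after the data are in.

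**Conclusion.** The point holds as a flaw in a stated rule. It should be fixed, but it does not stand in the way of the trial. The imprecision follows from the article's own numbers: ±0.73 at 14.4 completers per arm, ±0.65 with no dropout. The ambiguity over whether 36 is counted before or after dropout therefore changes nothing material.

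The misclassification rates rest on the assumed true effects, power and direct use of d, and they would soften if the investigators used judgement instead of the point estimate. Within those assumptions, roughly half to two-thirds of feasibility trials would lead to a size wrong by a factor of three or more, in either direction.

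**What to change.** Change the two sentences, in Statistical Analysis and in Outcomes, to say that:

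- between-group differences and Cohen d will be reported with 95% CIs as descriptive results, and the point estimate will not be the sizing target;
- the target difference for the powered RCT will be a justified smallest worthwhile difference, set in that trial's own protocol once its primary outcome is chosen;
- for sizing, this trial will supply the SD with its uncertainty, the correlation between baseline and 12 weeks, and the retention and missing-data rates.

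One way to allow for uncertainty in the SD is its upper one-sided 80% confidence limit. At about 27 degrees of freedom that is √(27/χ²₀.₂₀,₂₇) = 1.14 times the observed SD. Other conventions would also serve.

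The cost is two sentences and a few lines of analysis, with no change to recruitment, visits or data collection. The downside is that the future trial may come out larger: by about 30% (1.14² = 1.30) if that upper limit is used.

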### Ethical Considerations

Ethics approval was obtained from The University of Manchester Research Ethics Committee on August 18, 2023 (2023-17372-30569) to ensure that adequate safeguards are in place to protect the privacy of participants and to maintain the confidentiality of data. This study will be conducted in accordance with the UK Policy Framework for Health and Social Care Research and the Declaration of Helsinki guidelines. Prior to data collection, all the participants who agreed to participate in the study will sign a consent form, which includes a description of the study, its objectives, and participants’ involvement and rights (Multimedia Appendix 1). Participation in the study is entirely voluntary and participants can withdraw at any time. Participants will not receive financial compensation for their contribution to the study. Any deviations from the protocol will be put through the appropriate ethical amendment process. It is not anticipated that the study will be stopped prior to its intended end date. However, the study will be halted if safety issues arise regarding the intervention or resources to conduct the study are no longer available. Outcomes will be disseminated through conference presentations and publications in peer-reviewed journals in deidentified form. The findings will also be shared through presentations with digital inclusion teams and community stakeholders.

## Results

We anticipate recruitment will commence in March 2024 and will continue until enrollment is complete (N=36). The analysis is expected to be completed by November 2024, and the results will be published by January 2025.

## Discussion

### Principal Findings

The intervention (KOKU-Nut) involves educating users about how and why to make lifestyle changes, encouraging participation in regular and progressive strength and balance activities, and nudging older adults to improve their dietary intake. These features are underpinned by behavior change theories and have been co-designed with end users.

In comparison to many physical activity digital health tools such as Nymbl and Standing Tall, KOKU-Nut incorporates a nutritional component with a focus on dietary protein and fluid intake, given their low intakes among older adults [37,38] and their role in health [39,40]. The impact of diet is well established and can help older adults maintain health status and physical function [41]. Furthermore, it is estimated that one-quarter of Europeans older than the age of 65 years are at a high risk of malnutrition [42], and this can increase the risk of frailty, musculoskeletal conditions, and mortality [43-45]. In addition to the high prevalence of malnutrition, a recent James Lind Alliance priority setting partnership identified early intervention in vulnerable groups as a top priority [46].

There has been a rapid development in the number and quality of mobile health apps, and there is a growing acceptance among older adults. These tools have many benefits including that they can increase motivation through notifications and tracking of progress and provide personalized feedback to the user and increase engagement through gamification. However, there are still many challenges around introducing new digital health apps to this population. The usability of digital technology is important to ensure sustained use and to allow users to engage with the product for its intended purpose. Acceptability refers to the extent to which users consider the digital technology appropriate. Mobile apps are more likely to be usable and acceptable to older adults if they are codeveloped with them using principles of human-centered design [47,48]. KOKU-Nut was co-designed with end users and health care professionals, and we hope this will maximize the usability and usefulness of the interface and content.

This study will provide information on the feasibility and usability of the mobile health app KOKU-Nut. To our knowledge, this is the first digital health app in the United Kingdom designed to empower community-dwelling older adults to increase their activity levels and improve their diet and fluid intake so that they can stay active and healthy for longer.

### Study Limitations

This study has a number of limitations. We plan to recruit participants using purposive sampling from across Greater Manchester and thus this limits the generalizability of the results to the rest of the United Kingdom and internationally. However, this is a feasibility study that aims to inform a powered RCT that would then enable conclusions to be drawn. Furthermore, many of the study outcomes including dietary assessment and assessments of feasibility are self-reported and so prone to recall bias. Questionnaires will be checked for completeness and Intake24 appears to report similar data to intakes reported in interviewer-led dietary recall [49] and the gold standard assessment of energy intake using doubly labeled water [50].

### Conclusions

To our knowledge, this will be the first RCT to evaluate a digital health tool that nudges community-dwelling older adults living in the United Kingdom to improve their dietary intake and reduce the risk of malnutrition. The study aligns with guidelines developed by the Medical Research Council for developing a complex intervention by using qualitative and quantitative research to examine the barriers to intervention from the perspective of users and identify potential challenges around recruitment and retention [51].

## Appendix

Multimedia Appendix 1 Supplementary material to demonstrate SPIRIT checklist (S1), CONSORT checklist (S2) and Consent form (S3).

## Abbreviations

CONSORT: Consolidated Standards of Reporting Trials
KOKU: Keep-on-Keep-up
KOKU-Nut: Keep-on-Keep-up Nutrition
RCT: randomized controlled trial
SPIRIT: Standard Protocol Items: Recommendations for Interventional Trials
